### L-arginine clinical trial results.

1) Clinical trials in spinocerebellar degeneration

There have been no clinical trials of L-arginine in spinocerebellar degeneration.

2) Adverse effects in clinical trials and post-marketing surveillance for hyperammonaemia based on congenital urea cycle disorders and lysinuric protein intolerance.

In clinical trials conducted up to the time of approval, adverse reactions were observed in 5 (12.5%) 9 cases out of a total of 40 patients. The adverse reactions included increased AST (GOT) in 2 cases (5.0%), increased ALT (GPT) in 2 cases (5.0%), vomiting in 2 cases (5.0%), nausea/nausea in 1 case (2.5%), itching in 1 case (2.5%) and sleepiness in 1 case (2.5%). In the post-marketing surveillance, adverse reactions (including abnormal laboratory values) were observed in 24 cases (18 cases, 8.1%) out of 222 cases, the main adverse reactions being abnormal liver function in 4 cases (1.8%) and diarrhoea in 4 cases (1.8%) (at the time of the re-examination results).

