### Observations/test items

1. **Obtaining consent**

Record the date consent was obtained.

1. **Subject background**
2. Observation period: pre-registration

2) Observations: date of birth, gender, current medical history, complications

1. **Height**

1) Observation period: pre-registration

2) Observations: height

Measure without footwear or prosthetics.

1. **Body weight**

1) Observation period: pre-enrolment, start date, 48 and 52 weeks, and at discontinuation

2) Observations: body weight

1. **Vital signs**

1) Observation period: pre-enrolment, at start of treatment, 4, 8, 16, 24, 32, 40, 48 and 52 weeks, and at discontinuation

2) Observations: body temperature, blood pressure (systolic and diastolic), pulse

Resting blood pressure and pulse rate are measured in a sitting position. Measurements should be taken using the same arm (usually the arm opposite the dominant arm) and an appropriately sized cuff.

1. **Medication log**

1) Observation period: starting date, 4, 8, 16, 24, 32, 40 and 48 weeks, and at discontinuation

2) Observations: medication records

Distribution, collection and verification of medication diaries.

1. **Haematological examination**

1) Observation periods: pre-enrolment, start date, 4, 8, 16, 24, 32, 40, 48 and 52 weeks, (at *discontinuation)

2) Observations: red blood cell count, white blood cell count, white blood cell fractions (neutrophils, lymphocytes, monocytes, eosinophils, basophils) platelet count, haemoglobin, haematocrit values

1. **Blood biochemical tests**

1) Observation periods: pre-enrolment, start date, 4, 8, 16, 24, 32, 40, 48 and 52 weeks, (at *discontinuation)

2) Observations: AST, ALT, ALP, γGTP, LDH, CPK, serum creatinine, Na, K, Ca, Cl, P, BUN, triglycerides, total cholesterol, blood sugar at any time, CRP

1. **Urinalysis**

1) Observation periods: pre-enrolment, start date, 4, 8, 16, 24, 32, 40, 48 and 52 weeks, (at *discontinuation)

2) Observations: occult blood, protein, sugar, urobilinogen

1. **Pregnancy tests (performed only on female subjects of childbearing potential).**

1) Time of observation: pre-enrolment, date of administration

2) Observations: pregnancy test (urine hCG or serum hCG)

1. **Evaluation of SARA scores.**

1) Observation periods: pre-enrolment, start date, 4, 8, 16, 24, 32, 40, 48 and 52 weeks, (at *discontinuation)

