### Major adverse events foreseen in this trial

1. Nausea, nausea and vomiting
2. Diarrhoea
3. Feeling that one's skin is itchy
4. Abnormal liver function (increased AST, ALT, ALP)

The frequency of occurrence, calculated from the combined results of clinical trials and post-marketing surveillance up to the time of approval, ranged from 0.1% to less than 5% in all cases.

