## Response to adverse events.

### Dealing with anticipated adverse events.

In the event of an adverse event, the investigators and sub-investigators should provide appropriate first aid, pay attention to ensuring the safety of the subject, and endeavour to resolve and investigate the cause by having the subject undergo diagnosis and treatment by a specialist physician when necessary.

For each anticipated adverse event, take the following actions

1. For nausea, nausea and vomiting, careful follow-up or antiemetics should be administered according to symptoms.
2. For diarrhoea, careful follow-up or intestinal regulators should be administered according to symptoms.
3. Careful follow-up or anti-allergic agents should be administered for itching, depending on the symptoms.
4. If liver function abnormalities (increased AST, ALT, ALP) exceed three times the upper limit of the institutional reference value, the investigator (subcontractor) will inform the study coordinating investigator of the results of a thorough examination of the causal relationship with the investigational drug and discuss the need to discontinue the investigational drug.

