### Follow-up of adverse events that cannot be ruled out as causally related to the investigational drug

Adverse events occurring during the trial period should be followed up as far as possible until recovery occurs or the event is deemed no longer clinically necessary. The method of inpatient or outpatient visits, or in the case of outpatients, the frequency of visits and test items, etc., should be determined by the investigator or sub-investigator, depending on the type and severity of the relevant adverse event. However, if there is a reasonable reason to terminate the investigation in the middle of the study, the investigator or sub-investigator may terminate the follow-up investigation by stating the reason in the original documents such as the medical record.

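### Liver function is the one laboratory risk the protocol foresees and sets a threshold for, yet the fixed biochemistry list omits bilirubin, so no baseline or concurrent value is guaranteed

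*Protocol*

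**What the plan says.** Protocol 8.5.2 (Observations/test items, Blood biochemical tests) lists the analytes: "AST, ALT, ALP, γGTP, LDH, CPK, serum creatinine, Na, K, Ca, Cl, P, BUN, triglycerides, total cholesterol, blood sugar at any time, CRP". They are measured at pre-enrolment, on the start date, at weeks 4, 8, 16, 24, 32, 40, 48 and 52, and as far as possible at discontinuation. The haematology list in the same section holds blood counts only. Urinalysis includes urobilinogen but not bilirubin.

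Section 11.3.1 names four foreseen events. Three are symptoms (nausea and vomiting, diarrhoea, itching). The fourth is abnormal liver function, defined by rises in AST, ALT and ALP.

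Section 11.4.1 gives that fourth event the only numerical action rule of the four: "If liver function abnormalities (increased AST, ALT, ALP) exceed three times the upper limit of the institutional reference value", the investigator "will inform the study coordinating investigator of the results of a thorough examination of the causal relationship with the investigational drug", and the two discuss whether the drug should be stopped. No tests are named for this examination. For follow-up of adverse events, 11.4.2 says that "the frequency of visits and test items, etc., should be determined by the investigator or sub-investigator, depending on the type and severity" of the event.

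**The concern.** AST, ALT and ALP are enzymes and do not measure the liver's excretory function. Whether bilirubin rose with them helps to separate an isolated enzyme rise from impaired liver function. That distinction bears on both judgements required by 11.4.1: whether the drug was the cause, and whether to stop it.

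The scheduled data cannot supply this information for any subject in either arm. It depends on whether the individual investigator, at one of five sites, orders the test. Even then there is no pre-treatment value. A long-standing raised bilirubin could be read as a drug effect, and a transient rise at the time of the crossing could be missed.

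Safety is a stated objective, dosing lasts 48 weeks, and according to 3.2.5 L-arginine has not been tried before in this disease. The test list is protocol content, and a statistical analysis plan cannot analyse an analyte that was never measured.

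**Working it through.** The protocol states no figure on this point, so there is nothing to reproduce. The check is a reading of every laboratory list, followed by a rough size from the protocol's own rates.

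**1. Is bilirubin measured anywhere on schedule?**
- Biochemistry (8.5.2): 17 analytes, 0 of them bilirubin.
- Haematology (8.5.2): blood counts only.
- Urinalysis (8.5.2): occult blood, protein, sugar, urobilinogen.
- Schedule table (8.5.1): adds no analytes.

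**2. How many values are forgone?**
- Time points: pre-enrolment + start date + 8 later visits (weeks 4 to 52) = 10.
- With 40 subjects: 40 × 10 = 400 panels at most. If the pre-enrolment result is adopted as the start-date value for everyone, 40 × 9 = 360.
- Bilirubin values guaranteed now: 0.

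**3. Do the risk, the rule and the panel agree?** Section 11.3.1 uses AST, ALT and ALP, 11.4.1 uses the same three, and 8.5.2 measures all three at every scheduled biochemistry point. The rule can therefore fire as intended. The gap lies in what is known once it has fired.

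**4. How often might it matter?** Section 3.2.5 gives any-grade adverse reactions in other diseases: AST rise in 2 of 40 and ALT rise in 2 of 40 in the pre-approval trials, and abnormal liver function in 4 of 222 after marketing. The overlap between the AST and ALT cases is not stated, so the trial count is 2 patients (full overlap) to 4 (none).

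Pooled, this is (2 + 4)/262 = 2.3% to (4 + 4)/262 = 3.1%, in line with the under 5% stated in 11.3.1.

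For n = 20 active subjects, the expected cases are 20p and the chance of at least one is 1 − (1 − p)^20:

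| Source | p | Expected cases | Chance of at least one |
|---|---|---|---|
| Post-marketing, 4/222 | 1.8% | 0.36 | 30% |
| Pooled, 6/262 | 2.3% | 0.46 | 37% |
| Pooled, 8/262 | 3.1% | 0.61 | 46% |
| Trials, 2/40 | 5.0% | 1.0 | 64% |
| Trials, 4/40 | 10.0% | 2.0 | 88% |

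These rates cover any reported liver abnormality. The protocol gives no rate for values above three times the limit, which would probably be lower.

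**The case against.** The strongest reply is that nothing is broken. The foreseen event, the rule and the panel use the same three enzymes, and the safety outputs in 14.3.2 can be produced as planned. The rule already calls for a thorough examination, and 11.4.2 lets the investigator choose the tests, so bilirubin can be obtained when it is needed. The threshold refers to the institution's upper limit rather than to the subject's own baseline, and a bilirubin taken at the trigger could be read the same way. The panel also holds γGTP, LDH and CPK, with urobilinogen in urine. Serious liver disease is already grounds for exclusion, and the dose is within the approved range of a marketed product. Up to 400 values is a lot for less than one expected pooled case in the active arm, and a bilirubin required only at the trigger would serve the decision.

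Much of this stands. The omission is not a contradiction and does not touch the efficacy analysis. The number of cases in which bilirubin would change a decision is unknown and could be zero. The 88% figure assumes no overlap between AST and ALT cases and rests on the smaller source.

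Two points remain. A test ordered after a crossing cannot create a pre-treatment value, and because a crossing cannot be foreseen, only a value on each scheduled draw guarantees a concurrent one. The other liver-related tests give indirect information and do not replace serum bilirubin.

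**Conclusion.** The concern holds as a modest, inexpensive improvement to safety monitoring. No subject has a protocol-guaranteed bilirubin before or during treatment, although liver function is the only laboratory risk foreseen and the only one with a numerical action rule. The gain would be in reading a few individual cases, not in comparing the arms: about 0.46 to 0.61 expected any-grade cases among 20 active subjects on pooled data, and 0.36 to 2.0 across the separate sources. This assumes that rates from other diseases and treatment durations carry over. The view that bilirubin adds to the three enzymes is general clinical reasoning; the protocol does not state it.

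**What to change.** In 8.5.2, add total bilirubin to the blood biochemistry list at every scheduled draw, including pre-enrolment, with direct bilirubin measured if the total is raised. In the liver item of 11.4.1, require a bilirubin value in the information given to the coordinating investigator when AST, ALT or ALP exceeds three times the upper limit. The threshold and the decision process stay as they are.

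The cost is one more analyte on serum already drawn and one more data field, with no extra visit or needle and no change to sample size or significance level. The drawback is an occasional incidental, isolated bilirubin rise, in either arm, that will need explaining.

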### Investigational drug administration

The investigational drug (active drug or placebo) is packaged in polyethylene- aluminium foil laminate packets of 3 g each. The dose of the incestigational drug is 0.5 g per kg body weight as granules, administered orally in three divided doses per day for 48 consecutive weeks. The dose is determined according to body weight at the time of the pre-enrolment examination in accordance with Table 8.3.2 'Dosage Conversion Table by Body Weight', with the maximum dose at a body weight of 70 kg (11 packets/day). The investigational drug should be taken at approximately the same time of the day, morning, noon and evening. Investigational drug can be taken with anything other than water or with meals/snacks. Subjects should record their medication in a daily medication diary. The first oral dose of the investigational drug should be administered after the medical examination on Day 0, under the watchful eye of the investigator (subinvestigator) or collaborator.

If the investigational drug is vomited or spilled due to vomiting, do not take another dose as a replacement for it. If a dose cannot be taken at the scheduled dosing time due to a missed dose or a hospital visit, do not double the dose the next time, but take the scheduled single dose as soon as it becomes available, followed by an interval of at least two hours before resuming the next dose.

At the visit to collect the blood level measurement sample, the subject must be instructed to allow at least 6 hours between taking the investigational drug and collecting the sample. At the morning visit, do not take the study medication before or after breakfast. At the afternoon visit, do not take the incestigational drug before or after lunch. Any investigational medicines skipped for blood concentration measurement should be submitted to the investigator or collaborator as leftover medicines at the time of the visit. There is no need to take them together at the next oral dose.

Table 6.3.2 Internal dose conversion table by body weight （in Japanese）

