| AJA030 PK blood sampling ^#4^ |  |  |  | ○ | ○ |  |  | 〇 |  |  | ○ | ○ | <○> |
| Identification of adverse events^#5^ |  |  |  |  |  |  |  |  |  |  |  |  |  |
| Concomitant medications and therapies |  |  |  |  |  |  |  |  |  |  |  |  |  |

#1: Performed in female subjects of childbearing potential (if pregnancy test is performed with blood, draw approximately 2 mL more blood separately).

#2: If data from pre-registration testing is within one week of the start date of administration, the data may be adopted.

#3: Only cases from Niigata University Medical and Dental Hospital should be conducted.

#4: At the visit where the blood level measurement sample is collected, the subject must be instructed to allow at least 6 hours between taking the investigational drug and collecting the sample. At the morning visit, do not take study medication before or after breakfast. At the afternoon visit, do not take the investigational drug before or after lunch. Any investigational medicines skipped for blood concentration measurement should be submitted to the investigator or collaborator as leftover medicines at the time of the visit. There is no need to take them together at the next oral dose.

#5: Adverse event assessments at the start date of dosing are carried out after the administration of theinvestigational drug.

#6: Weeks 12, 20, 28, 36 and 44 will be telephoned by the site's clinical trial staff to check status and to confirm internal medication status. Tolerance is ±7 days.

<○>: If the investigational drug is discontinued during the investigational drug administration period, it will be carried out as far as possible.

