At the visit to collect the blood sample, the subject should be instructed to allow at least 6 hours between taking the investigational drug and collecting the sample. The site staff should confirm with the subject the date and time of the most recent dose of investigational drug prior to collection of the blood sample. Record the date and time of collection of the blood concentration specimen. The date on the case report form should be clearly recorded (e.g. DD MM YYYYY) and the time of collection should be recorded to the minute (HH:MM, 24-hour format).

1. **Identification of adverse events**

1) Observation period: starting date, 4, 8, 16, 24, 32, 40, 48 and 52 weeks, and at discontinuation

2) Observations: name of adverse event, date of onset, severity, severity, causal relationship to investigational, treatment, outcome and date of outcome

1. **Check concomitant medications and concomitant therapies**

1) Observation period: pre-enrolment, at start of treatment, 4, 8, 16, 24, 32, 40, 48 and 52 weeks, and at discontinuation

2) Observations: concomitant medications

Record the drug name (generic name), route of administration, dose, duration of administration and reason for concomitant use.
 Concomitant therapy

Record the name of the treatment, date and reason for implementation.

　(* when cancelled) should be carried out as far as possible, and the absence does not constitute a deviation from the plan.

If the data from the pre-registration test is within one week of the start date of administration, the data from the pre-registration test may be adopted as the data for the start date of the investigational drug administration.

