## Criteria for discontinuation of a clinical trial per subject.

The investigator or sub-investigator sh discontinue the subject's clinical trial in the following cases

1. If the subject withdraws consent to participate in the clinical trial

If consent is withdrawn for the use of all data, a consent withdrawal form should in principle be used, except in cases where it is difficult to come to the hospital. If only some of the survey items are withdrawn, a consent withdrawal form is not required and this should be recorded in the source documents.

1. When it is deemed difficult to continue the administration of the investigational drug to the subject concerned due to adverse events, etc.
2. Treatment that is deemed to have a significant impact on the outcome of the trial, such as the administration of surgical treatment during the trial period.
3. If a female subject becomes pregnant during the trial (if the male subject's partner becomes pregnant, the trial can continue)
4. If it is found after registration that the inclusion/exclusion criteria are violated.
5. If the subject is unable to continue the clinical trial for non-medical reasons (e.g. hospital transfer, relocation, etc.)
6. Other cases where the investigator or sub-investigator decides that it is difficult to continue the trial.

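### No pregnancy test is scheduled at the six visits where dosing could still be stopped (weeks 4 to 40), although pregnancy requires the drug to stop: a minor safety-schedule gap that is cheap to close.

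*Protocol*

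**What the plan says.** **Testing.** Protocol 8.5.2 (Pregnancy tests) applies to female subjects of childbearing potential, allows urine or serum hCG, and fixes the timing as "1) Time of observation: pre-enrolment, date of administration". The pregnancy row of Table 8.5.1, and the same row in the synopsis schedule, have marks at screening and day 0 and nothing at weeks 4 to 52 or at discontinuation. Footnote #2 of Table 8.5.1 adds: "If data from pre-registration testing is within one week of the start date of administration, the data may be adopted".

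**Dosing.** Section 8.3.2 has the drug "administered orally in three divided doses per day for 48 consecutive weeks".

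**Action on pregnancy.** Section 10.2 lists among the reasons to discontinue a subject: "If a female subject becomes pregnant during the trial". Section 11.7 requires the drug to be stopped immediately once a pregnancy is found, and the investigator to follow up to the birth.

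**What happens during dosing.** Adverse events are asked about at every visit: "Observation period: starting date, 4, 8, 16, 24, 32, 40, 48 and 52 weeks, and at discontinuation". Telephone calls at weeks 12, 20, 28, 36 and 44 are made "to check status and to confirm internal medication status". Urinalysis is scheduled at every visit but covers only "occult blood, protein, sugar, urobilinogen".

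**The concern.** A rule to stop at once works only as fast as the pregnancy is found. After day 0, nothing scheduled can find a pregnancy that the woman has not recognised. Adverse event enquiry and telephone calls depend on what she knows, and the urine taken at each visit is not tested for hCG. Discovery therefore rests on self-report or on an unscheduled test, and dosing may continue past the point at which the protocol wants it stopped.

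A second, smaller matter concerns the follow-up to birth in 11.7. With no test at or after the end of dosing, a pregnancy conceived in the last weeks of treatment may go unidentified, and its follow-up would then not be started.

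What is at stake is avoidable exposure of a foetus to the study drug and the completeness of pregnancy follow-up. The efficacy comparison is not touched.

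**Working it through.** The plan states no figure to reproduce. The check is a count from Table 8.5.1, followed by simple arithmetic.

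**Counts**
- Visits at which dosing can still be stopped: weeks 4, 8, 16, 24, 32, 40 = 6. Scheduled hCG: 0 of 6. Scheduled urinalysis: 6 of 6, and also at weeks 48 and 52.
- Contacts before week 48: 6 visits + 5 calls = 11, nominally every 4 weeks from week 4 to week 44. Scheduled hCG: 0 of 11.

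**Time from the last scheduled test to the end of dosing** (48 weeks = 336 days, from 8.3.2)
- Test on day 0: 336/7 = 48 weeks.
- Screening test adopted under footnote #2, up to 7 days earlier: (336 + 7)/7 = 49 weeks.

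**With tests at weeks 4 to 40**
- Longest untested stretch of dosing, nominal: 8 weeks.
- Maximum, when adjacent visits fall at opposite ends of their ±7-day windows: (56 + 7 + 7)/7 = 10 weeks.

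**Illustrative gain per pregnancy.** Assumptions, none of them from the protocol: conception time t is uniform over weeks 0 to 48; urine hCG turns positive L = 2 weeks after conception; the woman reports promptly on recognising the pregnancy, R weeks after conception.
- Self-report only: mean exposure = R − R²/96 weeks.
- With tests: dosing stops at the earliest of the first test at or after t + 2, t + R, and week 48.
- Tests acting alone: (6 + 16 + 4 × 48 + 50)/48 = 264/48 = 5.5 weeks.

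| Recognised at R | Self-report only | With tests | Saved (range for L = 1.5 to 3) |
|---|---|---|---|
| 4 weeks | 3.8 | 3.6 | 0.25 (0.39 to 0.06) |
| 8 weeks | 7.3 | 5.3 | 2.0 (2.4 to 1.4) |
| 12 weeks | 10.5 | 5.5 | 5.0 (5.5 to 4.1) |

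If a recognised pregnancy is reported only at the next four-weekly contact, the savings at L = 2 become 1.0, 3.5 and 6.5 weeks.

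**Illustrative trial-wide size.** Further assumptions, also not from the protocol: 1 to 5 women of childbearing potential on active drug, and a pregnancy rate of 1 to 5% per year on effective contraception.
- Exposed pregnancies: from 1 × 0.01 × 48/52 ≈ 0.01 to 5 × 0.05 × 48/52 ≈ 0.23 in the whole trial.
- Exposure avoided: from about 0.01 × 0.25 ≈ 0.002 weeks to about 0.23 × 5.0 ≈ 1.2 weeks.

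**Where the final test belongs.** With L = 2, a test at week 48 sees conceptions up to week 48 − 2 = 46 and misses those in weeks 46 to 48. A test at week 52 sees conceptions up to week 52 − 2 = 50. At the early end of its window it still reaches 51 − 2 = 49, which covers the whole dosing period.

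**The case against.** The strongest objection is that nothing here is an error. Sections 10.2 and 11.7 operate on any route of discovery, and no rule in the protocol asks for on-treatment tests. A light schedule also suits this product. It is a marketed amino acid dosed within the approved dosage (4.1). The rat studies in 3.2.4 report no foetal or teratogenic effect at about 2000 mg/kg/day in feed, and none on mating, pregnancy or foetus at 724 mg/kg/day subcutaneously. Pregnant women, and women who cannot consent to effective contraception, are excluded (5.2), and the site is in contact about every four weeks. Only half the subjects receive arginine. The gains tabulated above are per pregnancy, and the largest requires a pregnancy unrecognised for 12 weeks despite those contacts.

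Most of this stands and sets the severity. It does not remove the point, because none of these safeguards detects a pregnancy the woman is unaware of, and the protocol kept its stop rule despite the reassuring data.

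Some instructions may lie outside the text at hand. The consent pages are not shown, and 11.7 refers reporting to a separate safety procedure. Either could tell women to report a missed period or to be tested. Such an instruction would help, but reporting would still depend on the woman noticing.

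Three stronger readings are tempting and are not supported:
- **That the schedule contradicts the stop rule.** Neither 10.2 nor 11.7 promises serial testing.
- **That the untested span reaches 50 weeks,** by adding the ±7-day window at week 48. Section 8.3.2 fixes 48 consecutive weeks of dosing, so the span is 48 to 49 weeks.
- **That foetal harm is likely.** The non-clinical data in the protocol point the other way.

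**Conclusion.** The point holds as a minor gap in the safety schedule. From the last scheduled hCG to the end of dosing, 48 to 49 weeks pass with a test at 0 of the 6 visits where a positive result could still stop the drug. These counts come straight from the protocol and rest on no assumption.

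The benefit of testing does rest on assumptions. Per pregnancy it runs from about a quarter of a week of exposure avoided (recognition at 4 weeks) to about 5 weeks (recognition at 12 weeks). Across the trial the expected gain is very small, because few exposed pregnancies are likely. The number of women of childbearing potential among the 40 subjects is not stated. The change is worth making because it is nearly free and gives the protocol's own stop rule a means of detection. The trial is not unsound without it.

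**What to change.** For women of childbearing potential in both arms, amend 8.5.2 and both schedule tables as follows:
- Add urine hCG at weeks 4, 8, 16, 24, 32 and 40, on the urine already collected for urinalysis, with action on a positive result as in 10.2 and 11.7.
- Add a final urine hCG at week 52, where urinalysis is already scheduled, so that pregnancies conceived late in dosing are identified for the follow-up to birth in 11.7.
- For subjects who stop early, do this test at discontinuation on a best-effort basis. That matches the protocol's existing rule for urinalysis there, which "should be carried out as far as possible, and the absence does not constitute a deviation from the plan".

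**Cost.** 6 + 1 = 7 urine strips per completing woman of childbearing potential, the EDC fields, and a schedule amendment. Completers need no extra visit or sample. The drawback is an occasional false positive that has to be confirmed.
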